### Study 2: nested RCT

#### Subject selection and randomization

All participants in Study 1 will be stratified at one-month telephone follow-up into low and high scores on the MCS domain of the SF-12, (SF12-MCS), using the median cut point. We previously reported this as a transformed score of 55 [37], which is comparable to the same age-gender population SF-12 norms [41]. The nested RCT will be conducted involving only the subjects with lower than median SF12-MCS scores at this time point (Figure 1).

An independent trials office will randomize these subjects using a computer generated random number series, into an individualized person-centered community-based intervention, or ‘usual care’ which reflects no intervention. It is unlikely that any intervention would normally be offered to this population as it is not current practice to screen people for low mental component quality of life scores after an ED contact.

Considering Studies 1 and 2, there are three study cohorts (Figure 1):

•Subjects with SF12-MCS scores ≥55, who will be observed only, for 13 months after recruitment (12 months after the one month SF12 scores are taken) (the observed cohort)

•Subjects with SF12-MCS scores <55, from which two RCT groups will be allocated one month after recruitment, randomized into

•Intervention specifically tailored to address the individual’s problems, concerns, and goals (low SF12-MCS, intervention cohort)

•No treatment (low SF12-MCS, no treatment cohort).

Outcome measures for the two RCT groups will be taken at three-, six- and twelve-month time points after randomization (four, seven and thirteen months post-recruitment).

### The intervention

The intervention arm applies a novel person-focused home-based approach targeting individual need [45]. Patient/person-centered care has been defined by Berwick [46] as ‘The experience (to the extent the informed, individual patient desires it) of transparency, individualization, recognition, respect, dignity, and choice in all matters, without exception, related to one’s person, circumstances, and relationships in health care’ [46],p2].

The intervention will be applied independently by a large provider of community aged care in South Australia (Elderly Citizens Homes (ECH)). This group has developed a patient-centered program for community-dwelling older individuals considered by their GP to be at-risk of declining functionally. The program involves a home assessment and interview conducted by occupational therapists or physiotherapists to identify individual problems and concerns and to set appropriate goals. Care options are discussed with older people and families in particular individualized interventions, which could include attendance at day therapy centers, exercise, fitness, balance-retraining and/or socialization, organization of home help or community care packages, motivational interviewing or counseling. Transport to programs can also be provided to increase compliance and reduce attendance barriers. Programs can last three to fourteen weeks, depending on need. The median/person cost of the intervention approximates $2,100 (interquartile range (IQR) $350), which approximates the cost of one acute South Australian hospital bed-day.

### Ethical issues

Written permission has been obtained from the Hospital Executive and ED Management of the research site, and ethical approval has been granted by the Human Research Ethics Committee of the University of South Australia (Application ID: 0000031475).

While there are indications from its early evaluation data that the ECH intervention is acceptable to clients, its effectiveness is largely unproven, particularly in individuals with low SF12-MCS scores at commencement. We do not know that the intervention will provide any advantage; in fact, individuals may perceive that they are subjected to additional burdens, such as unwanted assessments and visitors in their home for (perhaps) no overall benefit. We see no disadvantage for the ‘control’ group (low SF12-MCS, no treatment cohort) at this point in our understanding, in not being offered care, nor not knowing that the intervention is available, as they are currently not offered routine intervention so early after an ED discharge. If ,however, at subsequent follow-up points (three, six or twelve months), any participant in the observed cohort arm or the low SF12-MCS, no treatment arm is identified as potentially demonstrating FD on any study measure, the need for rescue care will be suggested and ways to access this discussed. This may include attendance at their GP or making contact with local community service providers.

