#### Study 1: Longitudinal cohort study

The total sample is recruited in Study 1. Every participant will be assessed for FD outcomes and predictors over the following 13 months (at five time points) using a battery of tests.

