### Study 1 analysis

FD will be assessed as change from baseline at each time point as:

•One or more falls increase from the baseline rate

•More than one event of hospitalization, or ED presentation, from the baseline rate

•Decrease of one point in any item of the ADL instrument [18], or

•Decrease of 2+ points from baseline total iADL score [19], or any decrease in baseline score in the domains of home activities, doing laundry, shopping and getting places (we previously reported these domains as critical to functional independence) [37]

•Scores decreasing from above median at baseline in either physical or mental domain, to below median in the SF12 [41,42]

•Any decrease in AQoL_4D (in the manner recently described for chronic obstructive pulmonary disease (COPD))[44]

•Change to a more assistive gait aid (for example, a one point stick to a four-pronged stick)

•Change in living arrangements to more supported care

•Increased carer involvement

•Greater type and frequency of use of formal community services or informal supports

•More frequent GP attendances.

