The three study cohorts will be assessed at time of allocation into a study arm (one-month after recruitment) for homogeneity in key socio-demographic characteristics and immutable factors (for example, gender, age, schooling, postcode, diagnosis) and all outcome measures (including the percentage of ‘frequent flyers’ in each arm). We previously reported this as one or more ED contacts per month over the preceding 12 months [33,34].

Change over time in each outcome measure will be calculated using repeated measures analysis of variance (ANOVA) models, with study contact point, cohort (1, 2, or 3) and key demographic features as independent variables. Partial Least Squares (PLS) models using pathway analysis will be applied to the multiple outcome, immutable and mutable independent variables at each time point, to determine different spatial arrangements and the significant factors which impact on data clusters.

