### Hypotheses

As shown in Figure 2, our hypothese are:

1. The observed cohort will not demonstrate FD over the following 12 months in any FD measure.

2. The low SF12-MCS, no treatment cohort will demonstrate significant FD in any one or more outcome measures, taken over the next three months, when compared to their baseline recruitment status.

3. The low SF12-MCS, intervention cohort will show no FD (comparable findings to the observed cohort) over the next 12 months.

4. Additionally, those individuals in the low SF12-MCS, no treatment cohort who demonstrate significant FD at three months follow-up, and who access ‘rescue’ intervention (see Section on Ethics), will show an attenuated rate of FD over the following twelve months, compared with the rate they exhibited in the first three months.

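### Rescue advice sends flagged untreated participants to a GP or services, and the extra use then counts as functional decline, most clearly in hypothesis 4

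*Protocol article*

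**What the plan says.** - **Who is advised, and when (Ethical issues).** At the three-, six- and twelve-month follow-ups, participants in the observed cohort or the low SF12-MCS no-treatment cohort who are "identified as potentially demonstrating FD on any study measure, the need for rescue care will be suggested". The intervention cohort is not included.
- **What is advised (Ethical issues).** "This may include attendance at their GP or making contact with local community service providers".
- **How decline is scored (Study 1 analysis).** "FD will be assessed as change from baseline at each time point as" eleven listed criteria. One is "Greater type and frequency of use of formal community services or informal supports"; another is "More frequent GP attendances".
- **To whom this applies.** The list sits under Study 1, but Study 1 contains the whole sample: "Every participant will be assessed for FD outcomes and predictors over the following 13 months". The section Analysis of data from Studies 1 and 2 then compares the three cohorts: "Change over time in each outcome measure will be calculated using repeated measures analysis of variance (ANOVA) models".
- **What is predicted (Hypotheses).** Hypotheses 1 and 3 predict no FD over 12 months in the observed and intervention cohorts. Hypothesis 4 takes controls who declined by three months and then used rescue care, and predicts that they "will show an attenuated rate of FD over the following twelve months, compared with the rate they exhibited in the first three months".

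**The concern.** The trial advises some participants to do something that its own outcome definition counts as deterioration. The advice is directed at two of the three cohorts, and outcomes are measured again afterwards. A participant who follows it can be scored as declining at the next contact because they followed it, whatever has happened to their function.

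Three results are exposed:

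- the 6- and 12-month comparisons on GP and service use;
- any FD call that rests on those items alone;
- hypothesis 4, where someone who stabilises on every functional measure after rescue can still be scored as declining.

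On GP use the bias probably runs against the untreated cohorts. On service use its direction is uncertain, because the programme itself may arrange home help or care packages. In hypothesis 4 it runs against the hypothesis.

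**Working it through.** **Sequence of events (months after randomization)**

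| Contact | Before this contact, has advice been given? | Can compliance score as FD here? |
|---|---|---|
| 3 months | No | No |
| 6 months | Yes, at 3 months | Yes, on the GP and service items |
| 12 months | Yes, at 3 and 6 months | Yes, on the GP and service items |

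Advice given at 12 months follows the last measurement and has no effect. The other nine criteria, including ADL, iADL and SF12, do not have this scoring problem.

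**Hypothesis 4.** The reference period (the first three months) comes before any advice and the comparison period comes after it. The group is selected for having used rescue, so a rise in GP or service use is built into the second period. The comparison is within the no-treatment cohort, so service use arranged in the intervention arm cannot offset it.

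**Hypothesis 1.** The effect is marginal, because advice goes only to people already flagged on some measure.

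**Possible size on the GP item.** The protocol states no figure to reproduce. Only the 50 per arm comes from the document (Sample size considerations). These inputs are assumptions:

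- *q*, share meeting the GP item anyway in each arm: 20% or 30%.
- *f*, share of controls flagged: 30% or 50%. This is loosely anchored on the likelihood-of-FD figures at discharge under Pilot work, which measure something different.
- *u*, uptake among those flagged: 10%, 30% or 50%.

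Control rate = q + (1 − q) × f × u; intervention rate = q. For example, with q = 0.20, f = 0.50 and u = 0.30: 0.20 + 0.80 × 0.50 × 0.30 = 0.320.

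The table gives the probability of a significant control excess (pooled z-test, two-sided 5%, exact binomial enumeration) at u = 0.10 / 0.30 / 0.50.

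| q | f | Control rate | P(control excess) |
|---|---|---|---|
| 0.20 | 0.30 | 0.224 / 0.272 / 0.320 | 0.049 / 0.133 / 0.279 |
| 0.20 | 0.50 | 0.240 / 0.320 / 0.400 | 0.071 / 0.279 / 0.595 |
| 0.30 | 0.30 | 0.321 / 0.363 / 0.405 | 0.041 / 0.097 / 0.193 |
| 0.30 | 0.50 | 0.335 / 0.405 / 0.475 | 0.056 / 0.193 / 0.443 |
| either | no advice | equal rates | 0.025 to 0.026 |

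**Sensitivity to the assumptions (q = 0.20)**

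- *Programme also prompts GP visits* in 10% of its remaining participants: intervention rate 0.20 + 0.80 × 0.10 = 0.28. With f = 0.50 the control excess falls to 0.008 / 0.063 / 0.241. At 10% uptake an excess in the intervention arm (0.067) is then the likelier error.
- *All base positives are among those flagged* (f = 0.50, u = 0.30): newly positive = (0.50 − 0.20) × 0.30 = 0.09, control rate 0.29, P = 0.181.
- *Only half of compliers exceed their baseline visit frequency* (u = 0.50, so effective uptake 0.25): control rate 0.26 (f = 0.30) or 0.30 (f = 0.50). P falls from 0.279 to 0.107 and from 0.595 to 0.211.

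**Count-scale check, closer to the planned ANOVA.** Assume one extra visit per complier. The control mean then shifts by f × u, from 0.30 × 0.10 = 0.03 to 0.50 × 0.50 = 0.25 visits. Two-sample t-test at one time point, 50 per arm:

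| Assumed SD (visits) | Shift 0.03 | Shift 0.15 | Shift 0.25 |
|---|---|---|---|
| 1 | 0.035 | 0.112 | 0.235 |
| 1.5 | 0.031 | 0.071 | 0.128 |
| 2 | 0.030 | 0.056 | 0.090 |

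**The case against.** The strongest reply is that little of importance is touched. The trial is sized on iADL and SF12 at three months, before any advice, and those instruments do not have the scoring problem. What remains is two unpowered items of eleven at two later contacts, plus an additional hypothesis against which the bias works, so it cannot manufacture a success there. This is right, and it limits the severity. It does not remove the conflict, because the aims and hypotheses 1 and 3 make claims over 12 months.

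Other points on that side:

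- **Those advised are already flagged as FD.** On an any-item reading, a new false call needs the person to recover on every flagging item while GP or service use stays raised. This stands and narrows the effect on overall FD calls. It does not help the item-level comparisons, or hypothesis 4, where recovery elsewhere is the predicted result.
- **More GP visits in controls would be a real difference in use.** True. The error lies in labelling that use as decline, which the definition does.
- **The magnitudes are assumed and may lean high.** Also true. The half-threshold and count-scale results are much smaller than the upper end of the binary model, and one scenario reverses direction.
- **The programme can arrange services too,** possibly before three months. This is why no direction is claimed for the service item. It is another reason not to read that item as decline.
- **Follow-up assessors are blinded, so it is unclear how advice could be given by arm.** If every flagged participant were advised, the imbalance between cohorts would shrink. Hypothesis 4 would be unchanged.

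**Conclusion.** The concern holds, and it should be fixed. That the two items and hypothesis 4 can record compliance as decline follows from the text alone and needs no assumed figure. Hypothesis 4 is the clearest fault.

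How often the distortion would produce a misleading result is unknown. On the binary GP item a spurious control excess ranges from about 4% to 59% under the main assumptions, against a nominal 2.5%. It can fall to about 1% if the programme also prompts GP visits. The count-scale version gives about 3% to 24%. A two-proportion test or a single-time-point t-test is not the planned repeated measures model, so these figures show only what is possible. The three-month contrast and its stated 80% power are not in question.

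**What to change.** Leave the rescue provision as it is; it is an ethical safeguard.

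1. **Main change.** For the cohort comparisons and hypotheses 1, 3 and 4, define FD at all time points without GP attendance and without formal or informal service use. Report those items by cohort as resource use. Keep the full eleven-criterion definition as a sensitivity analysis.
2. **Helpful wording.** Describe the 6- and 12-month randomized contrasts as early programme versus usual care with rescue signposting.
3. **Helpful reporting.** Tabulate rescue advice and uptake by cohort.

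The first change is sufficient to remove the scoring conflict. The cost is analysis and reporting wording only, since Table 1 already records GP visits and formal and informal supports at every contact. The downside is that two genuine markers of dependence leave the main FD definition, and the 12-month claim becomes more modest.

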### Sample size considerations

To date, there is scant research that has established the effectiveness of any community-based person-centered intervention program that alerts older people who are on the cusp of FD to impending FD and provides means to assist and support them. We drew the likely effectiveness of the proposed intervention program from research on early intervention programs for at-risk older people who are in hospital or rehabilitation units. This included an Australian study [47] (significant improvement in goals and functioning) and a Dutch study [48] (effect size 0.25). We acknowledge that this research may not be readily generalizable to estimate effectiveness of the intervention in our reference population; however, it is the best available evidence for sample size calculation.

Our nested RCT study sample size was further calculated on minimal differences in iADLs and SF12 scores, expected at three-month follow-up from our pilot data [37]. These estimates are based on the three-month follow-up distributions for iADLs and SF-12. Parameters of power were set at π = 80% (1-β), with α = 5%. For iADLs, we identified that a minimum absolute effect size of 1.2 would be needed for participants to have dropped by at most 1 point on the Lawton scale (the Lawton definition of FD requires a drop of 2+ points on the scale). Thus, a minimum sample size of N_IADL_ = 50 per RCT cohort would be required (total 100). For the MCS domain of SF-12, a minimum absolute effect size of 4.3 would need to be observed, to put all scores above or equal to the median value, giving sample size of N_MCS_ = 30 per RCT cohort (total 60). Similarly for the PCS domain of SF-12, the minimum absolute effect size of 12.2 gives a sample size of N_PCS_ = 6 per RCT cohort (total 12). We require significance to be determined both clinically and statistically, so over-sampling is not of concern and, therefore, we choose the highest sample size (N_IADL_) of N = 50 per RCT cohort (100 total) at three months RCT follow-up (four months from ED recruitment). Thus, our continuing RCT sample at three months will reflect 100 individuals with low SF12-MCS (randomized 50 each into intervention and control arms), and 100 individuals with high SF12-MCS who will simply be followed-up.

To provide the nested RCT cohort sample, there are specific considerations which will influence the number of individuals invited to participate in Study 1:

•Eligibility at time of recruitment (12% continuation).

•Consent at time of recruitment (30% continuation).

•Continuity through study (43% continuation).

•Study-designed attrition (estimated 10% attrition).

•Increased awareness of the study purpose, through the previous successful relationship established between the research team and the Royal Adelaide Hospital (RAH) staff, regarding awareness of detecting the risk of FD (estimated as improving the capture rate of eligible individuals by 10%).

Thus, to provide a continuing sample of 200 total subjects (with high and low SF12-MCS) at three months follow-up, we require a continuing eligible sample at the one-month assessment point of 220+ individuals; therefore we require a sample of 570 eligible consenting individuals recruited on discharge from ED. Based on previous experience, this will take 14 weeks at the participating hospital.

For the nested RCT, we also took into account an assumed rate of refusal for the intervention of 1:10 individuals who are offered it. This figure is based on pilot feedback from ECH, the intervention provider. We will address a potential loss of power in our intervention arm, which would occur if eligible subjects refused, by replacing every second refuser in the intervention group with an individual randomly selected from the control group for the RCT, who was recruited at the same time as the refuser. By replacing 1:2 refusers (as opposed to 1:1), this retains the balance in the two intervention arms. We will also analyze the characteristics of the refusers qualitatively, to identify whether they are different from the individuals who agreed to participate in the intervention.

Intention to treat analysis will be used when data are missing. However, every effort will be made to minimize missing data. For instance when subjects are unable to be contacted at the agreed time for any one data collection point, we will note their data as missing; however, reasons for loss to follow-up will be sought by making further contact with the subject. If possible, replacement telephone interviews will be conducted within days of the missed appointment, to provide the missing information. When subjects provide some data during the telephone interview, but not all, reasons for missing information will be recorded, to determine the appropriateness of using ‘carry-forward last known value’.

### Analysis of data from Studies 1 and 2

The three study cohorts will be assessed at time of allocation into a study arm (one-month after recruitment) for homogeneity in key socio-demographic characteristics and immutable factors (for example, gender, age, schooling, postcode, diagnosis) and all outcome measures (including the percentage of ‘frequent flyers’ in each arm). We previously reported this as one or more ED contacts per month over the preceding 12 months [33,34].

Change over time in each outcome measure will be calculated using repeated measures analysis of variance (ANOVA) models, with study contact point, cohort (1, 2, or 3) and key demographic features as independent variables. Partial Least Squares (PLS) models using pathway analysis will be applied to the multiple outcome, immutable and mutable independent variables at each time point, to determine different spatial arrangements and the significant factors which impact on data clusters.

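### Moving randomised controls into the intervention arm to replace refusers breaks the randomisation and filters refusers out of one arm only

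*Protocol article*

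**What the plan says.** Under Subject selection and randomization, the protocol article states: "An independent trials office will randomize these subjects using a computer generated random number series". The two arms are the individualised programme and no intervention. Sample size considerations sets the trial at 100 people with low SF12-MCS, "randomized 50 each into intervention and control arms".

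The same section then assumes that 1 in 10 of those offered the programme will decline. To protect power it plans on "replacing every second refuser in the intervention group with an individual randomly selected from the control group for the RCT", the replacement being someone recruited at the same time as the refuser. It argues that replacing one refuser in two, and not every refuser, keeps the two arms balanced. The refusers' characteristics are to be compared qualitatively with those of people who accept.

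On the analysis population the section says only: "Intention to treat analysis will be used when data are missing". The analysis section enters cohort (1, 2 or 3) as a factor in repeated measures ANOVA. It does not say whether cohort means the arm assigned or the treatment received.

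**The concern.** Refusal happens after randomisation, and only people allocated to the programme have the chance to refuse. Ethical issues makes clear that controls are neither offered the programme nor told of it, so those among them who would have declined cannot be identified. Once the rule has been applied, arm membership depends on willingness to accept as well as on the random number series.

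Choosing the moved control at random does not cure this. It makes the mover typical of the control arm, but the filter still acts on one arm alone. The comparison becomes acceptors against a mixture of acceptors and would-be refusers. Willingness to accept home visits is plausibly related to function, motivation and mental quality of life, which the trial measures as outcomes. The protocol itself treats it as open whether refusers differ. What is at stake is the comparability that the nested trial was randomised to obtain.

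**Working it through.** **Inputs from Sample size considerations.** 50 per arm at three months; power 80%; alpha 5% (sidedness not given, two-sided assumed); 10% refusal; one control moved for every two refusers. The target is given as follows: "For iADLs, we identified that a minimum absolute effect size of 1.2 would be needed". The SD is not printed: "These estimates are based on the three-month follow-up distributions for iADLs and SF-12".

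**1. Implied SD.** The stated 50 per arm cannot be reproduced independently without an SD, so I solved for the SD that yields it:

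SD = 1.2 / [(1.960 + 0.842) × √(2/50)] = 2.14 (2.41 if the test is one-sided).

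The power figures below use 2.14 and the normal approximation.

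**2. What the balance claim implies.** With 50 per arm and R = 5 refusers:

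| Reading | Intervention | Control |
|---|---|---|
| All refusers leave, 1 in 2 replaced | 50 − 5 + 2.5 = 47.5 | 50 − 2.5 = 47.5 |
| All refusers leave, every one replaced | 50 − 5 + 5 = 50 | 50 − 5 = 45 |
| Only replaced refusers leave, 1 in 2 replaced | 50 − 2.5 + 2.5 = 50 | 50 − 2.5 = 47.5 |
| Refusers stay, movers added, 1 in 2 | 50 + 2.5 = 52.5 | 50 − 2.5 = 47.5 |
| Refusers become controls, 1 in 2 replaced | 50 − 5 + 2.5 = 47.5 | 50 + 5 − 2.5 = 52.5 |

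Of these, only the first gives equal arms with replacement of one in two, and full replacement on the same footing (second row) does not. The protocol's own claim therefore implies that all refusers leave the intervention arm. With 55 per arm (half of the 220 people required at one month are low scorers, split in two), the count is 55 − 5.5 + 2.75 = 52.25 against 55 − 2.75 = 52.25.

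**3. Composition after the swap.** Refusers are 0% of the intervention arm. In the control arm would-be refusers are about 10%, or 5/47.5 = 10.5% if every control who is moved accepts.

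**4. Bias when the programme does nothing.** Bias = share of would-be refusers in control × D, where D is the mean outcome gap between acceptors and refusers. The documents give no D, so the values below are assumptions. The type I error uses SE = 2.14 × √(2/47.5) = 0.44.

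| Assumed D (iADL points) | Bias, share 10% to 10.5% | As % of 1.2 | Two-sided type I error |
|---|---|---|---|
| 0.5 | 0.05 | 4% | 5.2% |
| 1 | 0.10 to 0.11 | 8% to 9% | 5.6% to 5.7% |
| 2 | 0.20 to 0.21 | 17% to 18% | 7.4% to 7.7% |
| 3 | 0.30 to 0.32 | 25% to 26% | 10.5% to 11.1% |

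Simulation with 55 per arm and SD 2.12 agrees (0.11, 0.19 and 0.31 for D of 1, 2 and 3). In the same simulation, analysis as randomised has a bias of about zero.

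**5. What the rule buys.** Power = Φ(effect/SE − 1.96).

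- Refusers dropped and one in two replaced, 47.5 v 47.5: Φ(1.2/0.4395 − 1.96) = 78.0%.
- Refusers dropped and none replaced, 45 v 50: Φ(1.2/0.4401 − 1.96) = 77.8%.

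**6. Analysis as randomised, no replacement.** If refusers get no benefit, the mean effect is 0.9 × 1.2 = 1.08.

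- 50 per arm: Φ(1.08/0.4283 − 1.96) = 71.3%.
- 55 per arm: Φ(1.08/0.4084 − 1.96) = 75.3%.
- For 80% power: 50/0.9² = 61.7, so 62 per arm (124 in total).

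**7. Keeping the rule but analysing as randomised.** The 2.5 treated controls are 5% of that arm, so the contrast falls further, to (0.90 − 0.05) × 1.2 = 1.02 points. Power with 50 per arm is Φ(1.02/0.4283 − 1.96) = 66%.

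**The case against.** The best reply has four parts.

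- **Removal is inferred.** The article never says outright that refusers leave the intervention arm's data or that moved controls are analysed as treated. An analysis plan might define the sets. This stands as a caveat, but the inference comes from the protocol's own balance claim. If refusers did stay, the arms would not be balanced as stated and moving controls would still override the allocation. Intention to treat does not rescue the rule: it is invoked for missing data only, and analysing as randomised after the swap lowers power further (step 7).
- **The direction of bias is unknown.** People may decline because they are coping well, which would bias against the programme. If refusers do not differ, the mean is unbiased. This stands. A 3-point gap is also large, about 1.4 SD (3/2.14), so the upper end of the range is an extreme.
- **Safeguards exist.** The moved control comes from the same recruitment period, refusers are compared with acceptors, the cohorts are checked for homogeneity at allocation, and demographic features enter the model. None of these removes selection on unmeasured willingness.
- **The fix is not free.** Analysis as randomised takes power below the stated 80%. This stands, and the choice it leaves belongs in the protocol.

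**Conclusion.** The concern holds and must be fixed before the nested trial is analysed as a randomised comparison. The rule lets behaviour after randomisation decide who is counted in each arm. The balance it keeps is numerical, not prognostic.

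The difference in composition is about 10 percentage points of would-be refusers. The resulting bias is about one tenth of the refuser gap: modest for small gaps, up to about a quarter of the target effect for a 3-point gap, and of unknown sign. More recruitment would not reduce it. Against this, replacement gains about 0.1 percentage point of power over simply dropping refusers.

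The conclusion rests on the protocol's 10% refusal figure and on the reading that refusers leave the intervention arm. The sizes rest also on the assumed gaps, a two-sided test, and the back-solved SD of about 2.14. The breach of allocation depends on none of the assumed sizes.

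**What to change.** Delete the replacement rule. State that every randomised person stays in the assigned arm and that the primary comparison is as randomised, whether or not the programme is accepted. State this separately from the handling of missing data. Say explicitly that refusers continue with the telephone assessments at four, seven and thirteen months; these are already planned for all participants, so no visits are added. Define cohort in the ANOVA as the arm assigned.

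If an effect in acceptors is of interest, a complier-average estimate with allocation as the instrument can be added as a secondary analysis. This is optional.

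Restate the power for 10% non-uptake: about 71% with 50 per arm and 75% with 55, and print the SD used. Removing the bias needs no more participants. Restoring 80% power would: about 62 per arm at three months, which scales the 570 recruits to about 707 (570 × 124/100). The sponsor should say which of the two it accepts. Otherwise the cost is protocol wording.
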